### Statistical analyses

All statistical analyses will be performed with the intention-to-treat set, the full analysis set and the per-protocol analysis set. The primary analysis will exclude patients who die within 48 hours after ROSC, missing data on serum NSE level at 48 hours and 72 hours, consistent with the study design and sample size calculation. Supplementary analyses will include all randomized patients, and missing data will be handled using multiple imputation techniques to address potential bias. A multiple imputation approach will generate multiple datasets with imputed values, which will then be analyzed using the same statistical methods described for the primary and secondary outcomes. The results will be compared with those from the complete-case analysis to ensure robustness.

Primary and secondary outcomes will be analyzed using mixed-effects models, with recruitment site included as a random effect to account for between-center variability. Covariates such as age, sex, initial arrest rhythm, total collapse time, underlying disease, and grade of revised post-Cardiac Arrest Syndrome for Therapeutic hypothermia score [21] will be included as fixed effects, particularly if imbalances are observed. Mixed-effects models provide a more conservative and reliable approach than simple t-tests, allowing for appropriate handling of multi-center data. Survival duration and time to awakening will be assessed by the Kaplan–Meier method and compared by the log-rank test. Subgroup analysis will be conducted by predefined groups according to age, sex, initial arrest rhythm, arrest cause, total collapse time, NSE level at 48 hours, grade of revised post-Cardiac Arrest Syndrome for Therapeutic hypothermia score, timing of first medication administration, vitamin C level, and thiamine level. Two-tailed P-values less than 0.05 will be considered statistically significant. Statistical analysis will be performed using SAS version 9.4 (SAS Institute, Cary, NC, USA), IBM SPSS for Windows, version 21.0 (IBM Corp., Armonk, NY, USA), and R (version 3.6.1; R Foundation for Statistical Computing, Vienna, Austria; https://www.R-project.org).

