## Materials and methods

### Study design

The steroid, thiamine, and ascorbic acid during the post-resuscitation period for comatose OHCA survivors (STAR) trial is a single-blind, multicenter, randomized placebo-controlled trial being conducted in nine emergency departments (EDs) of tertiary university-affiliated hospitals in South Korea. The institutional review board of all participating hospitals have reviewed and approved the study protocol, including the institutional review board of Asan Medical Center (No. 2021–0613, approved on April 27, 2021). The STAR trial is registered under clinicaltrials.gov as protocol NCT04921189 on June 4, 2021. The study started on December 31, 2021 and the estimated study completion date is June 5, 2025. The investigators have obtained written informed consent from all patients’ legal surrogates. The Ministry of Food and Drug Safety in Korea has also approved the trial protocol. All OHCA survivors are being screened for eligibility by the attending emergency physician. Fig 1 shows the study schedule and Fig 2 illustrates the study flow chart.

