### Randomization, treatment allocation, and blinding

The patients will be randomly assigned in a 1:1 ratio to either the treatment group or the placebo group. The randomization sequence will be generated by *R* (version 3.3.3; R Foundation for Statistical Computing, Vienna, Austria; https://www.R-project.org) with randomized blocks of 4, stratified by recruitment site. The allocation sequence will be concealed from the attending emergency physicians and researchers enrolling and assessing patients in sequentially numbered, opaque, sealed, and stapled envelopes. The envelopes will be opened only at the allocation time. Given that patients are in a comatose state, they cannot perceive or differentiate the treatment solution from the placebo. To ensure blinding, study medications and placebo solutions are prepared by independent, unblinded personnel who are not involved in patient care or outcome assessments. However, the research team responsible for patient care and administering the treatments is aware of the group allocation. The primary outcome of this study, peak NSE levels at 48 and 72 hours after ROSC, is an objective biomarker, reducing the risk of bias associated with unblinded personnel. Additionally, secondary outcomes will be assessed by blinded evaluators to further minimize potential bias.

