### Outcome measure

The primary outcome will be the peak NSE level at 48 or 72 hours after ROSC. If a patient dies before 48 hours, the patient will be excluded from the primary analysis. If a patient dies between 48 and 72 hours after ROSC, the NSE level at 48 hours will be used. Secondary outcomes will include as follows: ΔNSE level, Δ sequential organ failure assessment (SOFA) score, mortality (7-day, 30-day, 90-day, 180-day, in-hospital), time to death (days), length of intensive care unit (ICU) stays (days, up to 1 year), length of hospital stays (days, up to 1 year), ICU-free days within 14 days, time to awakening (days to neurological recovery, defined as Glasgow coma scale >13 after ROSC) and neurological outcomes (30-day, 90-day, 180-day). The ΔNSE level is the serial change in NSE level that reflects the severity of reperfusion injury during the post-cardiac arrest period (ΔNSE level = the peak NSE level at 48 and 72 hours after ROSC NSE level at 24 hours after ROSC). The Δ SOFA score is defined as the difference between the SOFA score at enrolment and the maximum SOFA score between 24 and 72 hours after ROSC (ΔSOFA score = initial SOFA score at enrolment − maximum SOFA score between 24 and 72 hours after ROSC). If a patient dies in the first 72 hours, the maximum SOFA score will be counted as 24. Neurological outcomes will be assessed using cerebral performance category scores and the modified Rankin scale at 30, 90, and 180 days after ROSC. A good neurologic outcome is defined as cerebral performance category scores of 1–2 and modified Rankin scale of 0–2, respectively.

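### The log-rank test for survival and awakening leaves out recruitment site, the randomisation stratum, and these outcomes are not exempted from the mixed-model sentence: a minor efficiency and clarity point

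*Protocol article*

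**What the plan says.** In the Protocol article, Outcome measure lists both "time to death (days" and "time to awakening (days to neurological recovery, defined as Glasgow coma scale >13 after ROSC" among the secondary outcomes.

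Statistical analyses gives a general rule: "Primary and secondary outcomes will be analyzed using mixed-effects models, with recruitment site included as a random effect to account for between-center variability". A list of example covariates follows, and these "will be included as fixed effects, particularly if imbalances are observed". The mixed model is then justified: "Mixed-effects models provide a more conservative and reliable approach than simple t-tests, allowing for appropriate handling of multi-center data". The next sentence turns to the two time-to-event outcomes: "Survival duration and time to awakening will be assessed by the Kaplan–Meier method and compared by the log-rank test". It mentions neither site nor covariates, and it does not say how it relates to the general rule.

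Patients are allocated 1:1 "with randomized blocks of 4, stratified by recruitment site", and the trial is "being conducted in nine emergency departments (EDs"). The Discussion says that the trial is powered for the primary outcome and that secondary results will be treated as exploratory.

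**The concern.** Site is the only stratification factor in the randomisation, and the plan itself argues that multi-centre data call for a site term. The test it then names for survival and awakening has none. Blocking within site forces near balance of the arms at each site, so the true variance of the treatment comparison is smaller than an unstratified variance formula allows. When sites differ in prognosis, the unstratified test therefore rejects too seldom and loses some power.

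There is also a gap in wording. Read literally, the general sentence covers every secondary outcome, including these two, and no clause sets them apart. A reader cannot be certain whether the log-rank test is the inferential analysis or accompanies a model. The supplementary multiple-imputation analyses are to reuse the methods described for the outcomes, so the uncertainty carries over to them.

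At stake is a little precision on two patient-relevant outcomes that would support a biomarker primary, in a trial that already concedes limited power for secondary outcomes.

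**Working it through.** **No plan figure applies.** Sample size calculation concerns peak NSE only (68 per group, and 68 / 0.85 = 80 after 15% dropout). The article gives no mortality, hazard ratio, event count, site variance or covariate strength for survival or awakening. From the article come n = 160, nine sites, 1:1 allocation, site-stratified blocks of 4 and two-sided alpha 0.05. Every other input below is an assumption.

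**Formulas.** The unstratified log-rank statistic is Z = Σ(O − E) / √ΣV, with risk sets over all patients. The stratified version forms O, E and V within each site and then sums. A test rejects when |Z| > 1.96. With 2,000 replicates, the simulation standard error is about √(0.75 × 0.25 / 2000) = 1.0 point for a power of 75%, and √(0.05 × 0.95 / 2000) = 0.5 point for a rejection rate of 5%.

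**Set 1.** Near-equal sites, exponential times censored at 180 days, 50% events at HR 1, true HR 0.5, no covariate effect:

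| Site SD (log hazard) | Power, unstratified | Power, stratified | Change | Null rejection, unstratified |
|---|---|---|---|---|
| 0 | 78% | 77% | -1 | 5.4% |
| 0.3 | 77% | 77% | 0 | 5.2% |
| 0.5 | 75% | 79% | +4 | 4.1% |
| 0.7 | 73% | 77% | +4 | 3.2% |

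Stratified null rejection was about 5%.

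**Set 2.** Patients spread at random over the nine sites, Weibull times (shape 0.5), control 180-day mortality about 55%, true HR 0.6, no covariate effect:

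| Site SD | Power, unstratified | Power, stratified | Change | Null, unstratified / stratified |
|---|---|---|---|---|
| 0 | 59.6% | 59.0% | -0.6 | 5.0% / 5.1% |
| 0.3 | 56.1% | 57.2% | +1.1 | 4.2% / 4.8% |
| 0.6 | 53.6% | 59.0% | +5.4 | 3.3% / 4.8% |

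Check on the first row by Schoenfeld's formula, power = Φ(√d × |ln HR| / 2 − 1.96): with d = 74.2 events, √74.2 × 0.511 / 2 = 2.20, and Φ(0.24) = 59%. This agrees.

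**Set 3.** Set 1's 50% events and HR 0.5, with equal and with unequal site sizes: null rejection of the unstratified test was about 3.5% to 4% at site SD 0.5 to 0.7. Stratifying changed power by about -1 to +6 points, and the loss stayed at about 1 point even with very small sites.

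**Type I error.** Over all nine null scenarios of Set 2, with and without a covariate effect, the unstratified test rejected in 3.3% to 6.4% of runs. The 6.4% arose with no site effect, and the stratified test gave 6.1% in the same runs, so it does not come from ignoring site.

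**Covariates.** In Set 2 with no site effect, unstratified log-rank against a Cox model adjusted for one prognostic covariate gave 59.6% against 59.3% at covariate SD 0, 48.0% against 59.0% at SD 0.7, and 37.0% against 60.6% at SD 1.2. The gain runs from nothing to about 24 points, according to a value that the article does not supply.

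**Limit.** These runs represent survival. None models time to awakening.

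**The case against.** A reader might infer that the plan sets two conflicting rules for the same outcomes. The text does not support that. The general sentence does not say that it covers all secondary outcomes, its justification contrasts mixed models with t-tests, and a specific sentence on time-to-event outcomes after a general one reads most naturally as a carve-out. What is missing is the exempting clause.

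A reader might also infer that the plan gives up, for these two outcomes, covariate precision that it secures for all the others, at a cost of some 8 to 18 points of power. Those figures compare the unstratified log-rank with a site-stratified, covariate-adjusted Cox model (69% against 77%, and 58% against 76%) under assumed covariate SDs of 0.7 and 1.0. They rest on a single, perfectly measured covariate in a correctly specified model. A real model would carry six listed covariates and nine sites on about 80 events (50% of 160) or fewer. The plan also ties covariates elsewhere to observed imbalance, so adjustment is not firmly promised for any outcome.

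It is fair to add that an unstratified log-rank test is valid, that mortality at fixed times and neurological outcomes remain under the site-adjusted rule, and that a condensed article may leave stratification and a hazard ratio to the full protocol or analysis plan. All of this lowers the weight of the point. It does not remove it: the article names a specific test without the design's stratum, while arguing in the same paragraph that a site term is the appropriate handling.

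**Conclusion.** The point holds as a minor matter of efficiency and clarity. The named test omits the randomisation stratum, and the two outcomes are not explicitly exempted from the mixed-model sentence. Under assumed inputs (50% events, HR 0.5, site SD of the log hazard 0 to 0.7), stratifying by site changes power by about -1 to +6 points; assuming HR 0.6 gives much the same range. A gain of 4 points or more appears only at a site SD of 0.5 or above. Any further gain from covariates cannot be sized from the article.

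There is no sign of inflated type I error from ignoring site. The unstratified test errs on the conservative side, at about 3% to 4% null rejection when sites differ strongly. The outcomes are exploratory, so no confirmatory conclusion depends on the choice.

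**What to change.** In Statistical analyses, or in the analysis plan:

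- State that the mixed-model sentence does not apply to time to death and time to awakening.
- Stratify the log-rank test by recruitment site for both outcomes, and keep the Kaplan–Meier curves as description.
- Report a hazard ratio with 95% CI from a Cox model with site as stratum or frailty.
- If covariate adjustment is wanted, name a small prespecified subset of the covariates already listed and treat that model as a supporting analysis, independent of observed imbalance.

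How deaths before awakening enter the awakening analysis is a separate question that this change does not settle.

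The cost is a few sentences. Site is known for every patient, so no new data are needed. The downside is about 1 point of power if sites do not differ.

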### Interventions

As soon as possible after achieving ROSC at the ED or arrival after achieving ROSC before ED admission, patients who meet inclusion criteria will be identified. After written consent is obtained from legal surrogates, a unique randomization number will be allocated to each participant in the order of enrolment. For the treatment group, ascorbic acid (50 mg/kg, maximum single dose 3 g, daily dose 6 g), thiamine (200 mg, daily dose 400 mg), and corticosteroid (100 mg, daily dose 200 mg) will be mixed in three separate 50mL bags of 0.9% saline, respectively, and administered through intravenous infusion over 60 min every 12 h for 3 days. For the placebo group, an identical volume of 0.9% saline (50 mL, respectively) will be administered through intravenous infusion over 60 min every 12 h for 3 days. The first administration of the study medication is aimed as soon as possible after ROSC, at least not to delay over 12 hours after ROSC.

All the participants will be treated with post-resuscitation care in accordance with the current guidelines [6,19,20]. Depending on the attending emergency physicians’ decision, in case of clinically suspected vitamin C, thiamine, or adrenal insufficiency, supplementation of ascorbic acid, thiamine, or corticosteroids is permitted. For patients requiring high dose vasopressors, corticosteroid administration is permitted based on the attending physician’s judgment. If the legal proxy requests withdrawal from the trial, the collected data and blood samples will be removed.

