### Data collection

T_ROSC24_, T_ROSC48_, and T_ROSC72_ indicate the time points of 24, 48, and 72 hours after ROSC, respectively. T_0_ is the time point of the first drug administration, which will aim to be administered within 12 hours after ROSC. The patients will receive the medication every 12 hours after T_0_, six times. T_ROSC24_ is between T_12_ and T_24._ Blood samples for plasma ascorbic acid and thiamine levels will be collected at enrolment prior to study drug administration and 72 hours after ROSC which will be transferred to the central laboratory for analysis. Blood samples for neuron-specific enolase (NSE) levels will be collected at 24, 48, and 72 hours after ROSC, and analyzed at the local laboratory of each participating hospital. A laboratory medicine specialist in all participating academic hospitals will assess the hemolysis index before reporting NSE values to ensure accurate NSE levels. Other blood samples will be collected at enrolment prior to study drug administration and daily for 3 days. We plan to collect and store serum samples at the same time, which will be frozen at -80°C immediately for future biomarker analysis. Adverse events and survival data will be monitored daily during hospitalization. The investigators will be blinded to the study group assignments and will conduct follow-up telephonic interviews for survival and neurocognitive function after hospital discharge around days 30, 90, 180, and 365.

An independent monitoring officer at the coordinating center will monitor the study procedures and data quality according to the Korea Good Clinical Practice guidelines in all participating centers. All data will be anonymized and collected using standard clinical report forms by investigators at each participating hospital. The monitoring officer will review and verify all data from inclusion to follow-up. The data will be stored at the coordinating center.

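### The predefined subgroup by 48-hour NSE splits patients on a post-treatment component of the primary outcome, so its treatment-effect estimates are biased

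*Protocol article*

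**What the plan says.** The Outcome measure section states: "The primary outcome will be the peak NSE level at 48 or 72 hours after ROSC". For some patients the outcome is the 48-hour value alone: "If a patient dies between 48 and 72 hours after ROSC, the NSE level at 48 hours will be used".

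The Statistical analyses section then predefines subgroup analyses by ten factors, including "arrest cause, total collapse time, NSE level at 48 hours, grade of revised post-Cardiac Arrest Syndrome for Therapeutic hypothermia score". It gives no cut-point for the 48-hour NSE and does not say to which outcomes the subgroups apply.

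On timing, the Interventions section asks that the first dose come as soon as possible and "at least not to delay over 12 hours after ROSC". The Data collection section adds: "The patients will receive the medication every 12 hours after T_0_, six times". On sampling it says: "Blood samples for neuron-specific enolase (NSE) levels will be collected at 24, 48, and 72 hours after ROSC". It lists no NSE sample before the first dose.

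The same subgroup list ends with "timing of first medication administration, vitamin C level, and thiamine level".

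**The concern.** A treatment effect within a subgroup is protected by randomisation only if treatment cannot change who belongs to the subgroup. Here the trial's own hypothesis is that treatment lowers NSE. If that is true, treated patients move from the high-NSE to the low-NSE subgroup. Treated patients in the low subgroup then include some who would have been high on placebo, and treated patients in the high subgroup are those whose NSE stayed high despite treatment. In both subgroups the treated patients are inherently sicker than the controls they are compared with.

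The subgroup variable is also part of the outcome, and for deaths between 48 and 72 hours it is the same number. At stake is the reading of a predefined analysis. A real effect could look weak in every subgroup, or look confined to patients with severe injury when it is uniform. The Discussion already cites a significant age subgroup, from an earlier before-after study without a significant overall result, as pointing towards a personalised approach. An artefact here could be read the same way.

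**Working it through.** **1. Is the 48-hour sample taken after treatment?** With the latest permitted first dose, at 12 hours after ROSC, and dosing every 12 hours, doses fall at 12, 24 and 36 hours. So at least three precede the 48-hour sample. The 24-hour NSE also follows at least one dose.

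**2. The plan's own figures.** The Sample size calculation section gives a mean peak NSE of 114, an SD of 119 and a 50% reduction, which is a difference of 57. Then n per group = 2 × (1.960 + 0.842)² × (119/57)² = 68.4, against 68 stated, and 68/0.85 = 80, as stated. The inputs are therefore the ones the plan used, on the untransformed scale.

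**3. Model for the illustration.** These are assumptions, not in the documents:
- NSE at 48 and 72 hours is log-normal, with equal medians m and equal log-SD s at both times.
- m and s are chosen so that the control peak, max(48 h, 72 h), has mean 114 and SD 119.
- Treatment halves both values in every patient.
- The cut is 60 ng/mL, the only NSE threshold the article names, and there it is a prognostic threshold.

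**4. Who falls in the low group.** Control share = Φ[ln(60/m)/s]. Because treated values are halved, treated share = Φ[ln(120/m)/s]. The treated low group therefore takes in everyone whose untreated 48-hour value is up to 120, while the control low group stops at 60.
- Correlation 0.70: m = 60.0, s = 0.897. Control Φ(0.00) = 50%; treated Φ(0.77) = 78%.
- Correlation 0.95: m = 70.7, s = 0.865. Control Φ(−0.19) = 42%; treated Φ(0.61) = 73%.

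**5. Apparent effect on mean peak NSE** (numerical integration; the true effect is 50%, or 57 units, overall)

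| Correlation | Low: control, treated | Difference (share of 57) | Reduction | High: control, treated | Difference (share of 57) | Reduction |
|---|---|---|---|---|---|---|
| 0.50 | 60.9, 39.7 | 21.1 (37%) | 35% | 175.7, 126.7 | 49.0 (86%) | 28% |
| 0.70 | 52.1, 36.9 | 15.3 (27%) | 29% | 175.9, 128.6 | 47.3 (83%) | 27% |
| 0.95 | 40.6, 31.9 | 8.6 (15%) | 21% | 168.2, 124.7 | 43.5 (76%) | 26% |
| 0.99 | 37.9, 30.5 | 7.5 (13%) | 20% | 164.1, 121.0 | 43.0 (76%) | 26% |

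**6. Sensitivity** (simulation, correlation 0.5 to 0.99 unless stated)
- Split at the pooled median: reductions of 18–33% (low) and 28–33% (high).
- Middle tertile: 5–23%. The two middle quartiles: 3–25%.
- Normal model with a uniform shift of 57, correlation 0.5 to 0.95, cut at 60 or the median: 36–59% of the shift remains in each subgroup.

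A subgroup factor fixed before the first dose would show the full 50% reduction in every stratum under the same uniform effect.

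The model leaves out covariate adjustment and the exclusion of deaths before 48 hours.

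**The case against.** **It is one factor of ten, and the primary analysis does not use it.** This stands. The primary estimate, sample size, randomisation and safety monitoring are untouched, which is why the point is not rated higher. The Discussion also says that secondary outcome analyses will be treated as exploratory, but it does not mention subgroups, so that caution covers this analysis only in part.

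**The article condenses a fuller plan.** This could excuse the missing cut-point and test. It does not excuse the choice of variable, which the article states outright and which no cut-point repairs.

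**The subgroups might be meant for other outcomes.** The text does not restrict them, so the primary outcome is included. For survival or neurological outcome the 48-hour NSE would not be part of the outcome, but it would still be measured after treatment and open to change by it. The figures above apply to peak NSE only.

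**Stronger readings.** A reader might infer that the effect would be roughly halved in every subgroup. That describes percentage reductions with a two-way split, and the normal model. It fails on the absolute scale with skewed NSE, where the low group loses most of the difference and the high group about a fifth, and it fails in middle tertiles or quartiles.

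A reader might also infer that the vitamin C and thiamine subgroups are biased. The article says: "Blood samples for plasma ascorbic acid and thiamine levels will be collected at enrolment prior to study drug administration and 72 hours after ROSC". A pre-dose sample therefore exists, and nothing says that the 72-hour level will define the subgroups. The time point is merely unstated.

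Timing of the first dose is set by a team that knows the arm, but both arms are infused on the same schedule and nothing in the article suggests that timing would differ by arm. How subgroup differences will be tested is ordinary content for an analysis plan.

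**Conclusion.** The point holds for the 48-hour NSE factor. As written, the plan conditions on a post-treatment component of the primary outcome, and the resulting subgroup estimates cannot be read as treatment effects. That conclusion needs no distributional assumption beyond treatment having some effect on NSE.

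The size does rest on assumptions. Under the log-normal model, with correlation 0.70 to 0.95 and a cut at 60 ng/mL, a uniform 50% reduction shows as about 21–29% in the low group and 26–27% in the high group. In units, about 9–15 of 57 remain in the low group and 44–47 in the high group, which would look like an effect confined to severe injury. Other cut-points, scales and correlations change the amounts.

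Severity: should fix. The primary analysis is not affected.

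**What to change.** Delete the 48-hour NSE from the list of treatment-effect subgroups. Do not replace it with the 24-hour NSE, which is also drawn after the first dose. Keep factors fixed before the first dose, such as age, sex, initial rhythm, total collapse time and the severity grade, all already listed.

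As a minor clarification, state that the vitamin C and thiamine subgroups use the enrolment sample taken before dosing.

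The cost is one edited sentence. It needs no new data and no change to sampling or sample size, and it should be made before any analysis by arm.
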